# Efficacy of Bioenergetic Health Index to Predict Delirium After Major Abdominal Surgery in Elderly Patients: A Protocol for a Prospective Observational Cohort Study

**DOI:** 10.3389/fmed.2022.809335

**Published:** 2022-04-25

**Keywords:** postoperative delirium, elderly patients, BHI, mitochondrial function, major abdominal surgery

## Abstract

**Introduction:**

Postoperative delirium (POD) is a common disorder following surgery, which seriously threatens the quality of patients’ life, especially the older people. The multifactorial manner of this syndrome has made it hard to define an ideal method to predict individual risk. Mitochondria play a key role in the process of POD, which include inflammatory on the brain caused by surgeries and aging related neurodegeneration. As BHI (Bioenergetic Health Index) could be calculated in cells isolated from an individual’s blood to represent the patient’s composite mitochondrial statue, we hypotheses that HBI of monocytes isolated from individual’s peripheral blood can predict POD after major non-cardiac surgery in elderly patients.

**Methods and Analysis:**

This is a prospective, observational single-blinded study in a single center. 124 patients aged ≥ 65 years and scheduled for major abdominal surgery (>3 h) under general anesthesia will be enrolled. Preoperative and postoperative delirium will be assessed by trained members using Confusion Assessment Method (CAM). For patients unable to speak in the ICU after the surgery, Confusion Assessment Method for the Intensive Care Unit (CAM-ICU) will be used. All patients will undergo venous blood sampling twice to measure BHI (1–2 tubes, 5 ml/tube): before the surgery and 1 day after surgery in wards. After discharge, patients will be contacted by telephone 30 days after surgery to confirm the incidence of post-discharge complications. The severity of complications will be categorized as mild, moderate, severe or fatal using a modified Clavien-Dindo Classification (CDC) scheme.

**Ethics and Dissemination:**

The study has been approved by the Ethics Committee on Biomedical Research, West China Hospital of Sichuan University, Sichuan, China (Chairperson [name], No. 2021-502). Study data will be disseminated in manuscripts submitted to peer-reviewed medical journals as well as in abstracts submitted to congresses.

**Clinical Trial Registration:**

[www.ClinicalTrials.gov], identifier [ChiCTR2100047554].

## Summary

1.To the best of our knowledge, no cohort study describing association between mitochondrial function and postoperative complications, and findings may promote clinical use of mitochondrial tests.2.This is the first study to connect the perioperative mitochondrial function of monocytes isolated from an individual’s blood with POD.3.This study was a single-center study and the sample size was relatively small.

## Introduction

### Background

Postoperative delirium (POD) is a cognitive disturbance characterized by acute and fluctuating impairment in attention and awareness. It commonly occurs between postoperative days 2–5. In the general surgical population, the incidence of postoperative delirium is reported to be 2.5–3% (1, 2). In patients aged more than 60–70 years, the incidence of postoperative delirium is considerably higher at 10–20% (3–5). Advancing age with decreased reserve and changes to the physical characteristics of the brain, including cerebral atrophy and changes in white matter, was associated with an increased risk of developing delirium (6–8). The severity of POD varies from individual to individual. Cognitive function changes may last for a few days, months or years, and there is a possibility of further deterioration (9). The occurrence of postoperative delirium lengthens hospital stay by 2–3 days and ICU stay by 2 days (10–12). Postoperative delirium is also associated with a 30-day mortality of 7–10%, compared with 1% in those without delirium (11–13).

Early identification of patients at high risk for delirium before surgery aids the clinician and allows for the development of strategies targeted at minimizing the occurrence of delirium. However, the multifactorial occurrence of POD makes it hard to foresee delirium even in fields with high incidence like cardiac surgery (14), and the tools for the prediction of delirium have shown to be insufficient (15). Potential blood markers can be divided into two categories: proinflammatory proteins and neuronal cell damage markers. Proinflammatory proteins are highly sensitive while with low specificity for the diagnosis or prediction of delirium, including IL-1, IL-6, C-reactive protein (CRP), interleukin, procalcitonin (PCT), and TNFa (16). Neuronal cell damage markers like protein S-100 and neuronal specific enolase (NSE) can only indicate an already ongoing detrimental process without any predictive ability. Beside blood markers, numerous risk prediction models are available for predicting delirium, including Katznelson, the original PRE-DELIRIC, and the international recalibrated PRE-DELIRIC model (13, 15, 17). But these models were formulated based on identified risk factors for patients in ICU (17). Validated prediction model for surgical patients is still lacking. All these limitations point to the need for better alternatives to assess preoperative risk of POD.

Understanding the potential role of mitochondria in POD pathophysiology is of importance due to the increase in our understanding of aging and inflammation. As cellular bioenergetics factories, the primary function of mitochondria is to generate ATP through electron transport chain and oxidative phosphorylation; however, this process is also accompanied by generation and release of reactive oxygen and nitrogen species (ROS, RNS) (18). Accumulation of ROS and oxidative damage is one of the cellular hallmarks of aging. As an extension of the free radical theory, the mitochondrial vicious cycle theory of aging emphasizes and refines the central role of mitochondria in the aging process (19). On the other hand, mounting evidence indicates that systemic inflammation on the brain caused by surgeries is the key process of the pathogenesis of POD (20). The impact of systemic inflammation on the brain can be profound. Neurons are highly vulnerable to the harmful effects of these reactive species due to its high metabolic rate, the predominance of fatty acids with a tendency to peroxidation, high intracellular concentrations of transition metals capable of catalyzing the formation of reactive oxygen species (ROS), and low levels of antioxidants (21). Systemic oxidative stress was associated with blood–brain barrier disruption and increased odds of developing postoperative delirium (22).

In central nervous system (CNS), mitochondrial dysfunction characterized by a progressive accumulation of mtDNA mutations, increased ROS production and impaired mitochondrial respiration, all of which have been shown to impair adult neurogenesis (23, 24) and result in neurodegenerative diseases (25, 26). Studies have proven that mitochondrial dysfunction is connected with neurodegenerative diseases, particularly in Parkinson’s disease (PD) (26), Alzheimer’s disease (AD) (25) and dementia. As an acute cognitive impairment, POD is closely related to these diseases in molecular pathways (27), which indicate us mitochondrial dysfunction also act as a key role in POD. And animal studies of elderly rats did prove mitochondrial dysfunction and oxidative stress contributes to the process of POD (28). In addition to be a main source of ROS, mitochondria are the prime targets of oxidative damage, which in turn reduces mitochondrial efficiency and leads to the generation of more ROS in a vicious self-destructive cycle (28, 29). Especially for elderly patients with chronic comorbidities, the pre-existing mitochondrial dysfunction make them more sensitive to perioperative changes (30). These findings suggest us mitochondria is the connection of inflammation and POD and the assessment of mitochondrial function may provide us with a clue to predict postoperative outcomes in aging patients.

Traditionally, the test of brain mitochondrial function needs fresh tissue samples, which limits its clinical use. However, the BHI (Bioenergetic Health Index), which proposed by Chacko et al., could be calculated in cells isolated from an individual’s blood to represent the patient’s composite mitochondrial profile (31). This advantage makes it possible for BHI developing to be a clinical test. Platelets, lymphocytes and monocytes are exposed to many soluble circulatory factors associated with metabolic stress and are, therefore, an ideal surrogate for determination of BHI in patients. Among which, monocytes are phagocytic cells which survey the body for sites of inflammation and play an essential role in the innate immune system (32–34). The clinical test carried out by Chacko et al. did prove that BHI was a sensitive measure of oxidative stress in human monocytes (35). Then, their following clinical study demonstrated that the BHI is significantly depressed in monocytes isolated from the post-operative pericardial fluid and blood of patients undergoing cardiac surgery (36). These findings suggest BHI is a functional biomarker of the impact of perioperative systemic oxidative stress. In brief, the BHI of monocytes in peripheral blood can reflect brain mitochondrial function and surgical systemic oxidative stress. Thus, we suppose the BHI can serve as a marker or predictor of POD. As there is no study to confirm the relationship between them, we conducted this study to test if HBI of monocytes isolated from individual’s peripheral blood can predict delirium after major non-cardiac surgery in elderly patients.

### Hypothesis and Objectives

We hypothesis that poor mitochondrial function with aging process makes brain vulnerable to systemic inflammation by surgeries. As BHI of monocytes in peripheral blood can reflect brain mitochondrial function and surgical systemic oxidative stress, we assume patients with low BHI have higher risk of POD.

The main objective of the current study was to find whether HBI of monocytes isolated from individual’s peripheral blood (preoperative or postoperative) can predict delirium after major non-cardiac surgery in elderly patients during hospitalization. The secondary objective was to determine whether BHI can predict moderate or severe complications within 30 days after surgery, because these events are also associated with perioperative inflammation/oxidative stress and poor organ function.

## Methods and Analysis

### Trial Design

This is a prospective, observational single-blinded study being conducted in a single center. The flowchart of this trial is in Figure 1. The study will include patients scheduled for major abdominal surgery (> 3 h) under general anesthesia in the operating center of West China Hospital of Sichuan University, Chengdu, China from July 2021 to December 2021.

**FIGURE 1 F1:**
[figure not shown]
Flowchart of the study.

### Ethics Approvals and Registration

Ethic approval for this study has been obtained from the Ethics Committee on Biomedical Research, West China Hospital of Sichuan University, Sichuan, China (Chairperson [name], No. 2021-502). The trial was registered at Chinese Clinical Trial Registry (ChiCTR2100047554). Participating sites obtained written informed consent by participating patients or their legal surrogates in accordance with local/national legislations. Fully data will be upload on the Clinical Trial Management Public Platform.

### Recruitment of Patients and Blinding

The patients will be recruited from the department of surgical ward in West China Hospital of Sichuan University. Patients undergoing major abdominal surgery under general anesthesia will be included in the study after obtaining informed consent. Before the surgery, investigators will identify suitable patients and approach them by telephone between 1 day and 1 week before surgery. Informed consents will be provided and interpreted by trained investigators, and they will be informed that their peripheral blood samples will be taken in this study. Once participants signed the consents, they will be enrolled and anonymized by an identification code. The subjects can voluntarily withdraw from the trial at any time. The BHI tests will be carried out by a skilled investigator. Preoperative delirium assessment and postoperative follow-up will be performed by trained members of the research team respectively, and they will be blinded to the outcomes of each other. Patients will be free to withdraw from the study at any time for any reason without prejudice to future care, and with no obligation to provide the reason for withdrawal.

***Inclusion criteria:*** (1) patients aged over 65 years, (2) no limitation of gender, (3) American Society of Anesthesiologists (ASA) physical status I–III, (4) mentally competent, (5) Informed and written consent.

***Exclusion criteria:*** (1) known hematological diseases, (2) long term use of sedative or psychotropic drugs, (3) unstable mental state, (4) history of allergy to anesthetics, (5) with learning difficulties, or mentally handicapped, (6) hemodynamic instability, (7) organ transplant surgery.

### The Bioenergetic Health Index Test

#### Blood Collection

All patients will undergo venous blood sampling twice to measure BHI (1–2 tubes, 5 ml/tube): before the surgery in the operating room and 1 day after surgery in wards. Blood was collected in vacutainers (BD Biosciences) containing 1.5 ml of ACD (acid citrate dextrose) solution (trisodium citrate, 22.0 g/l; citric acid, 8.0 g/l and dextrose 24.5 g/l). Blood samples need to be preserved temporarily at 4^°^C and send to the laboratory within 30 min.

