### Outcome Measures

#### Primary Outcome

Trained members of the research team will assess patients for delirium use the Confusion Assessment Method (CAM) (40) or the Confusion Assessment Method for the Intensive Care Unit (CAM-ICU) (41) for patients who are unable to speak (e.g., still intubated) in the ICU. These methods (CAM and the CAM-ICU) are reliable and have been consistent with the Diagnostic and Statistical Manual of Mental Disorders, 4th edition diagnostic criteria for delirium (42). The severity of delirium will be assessed by the maximum daily score of the CAM-S, a severity scale for patients who screen positive for delirium based on the CAM.

Before the surgery, investigators will identify suitable patients and approach them by telephone between 1 day and 1 week before surgery. Those who consented will be performed delirium assessments 1 day before surgery. After the surgery, delirium assessments were done when patients could be aroused sufficiently (Richmond Agitation and Sedation Score –3 or higher) (43). Investigators will assess delirium twice per day from the first to the third postoperative day in the morning and afternoon. The new onset of delirium after the third postoperative day will be assumed to be unrelated to anesthetic or other intraoperative factors.

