### Sample Size and Statistical Analysis

The sample size calculation was based on comparing the area under the curve (AUC) of the receiver operating characteristic (ROC) curves using MedCalc (Version 19). Assuming an outcome event rate of 9–11% (based on our previous study), a moderately good AUC of 0.8 for the BHI, a sample size of 112 patients had 90% power to detect this clinically relevant difference in AUC values (2-sided alpha of 0.05). To account for 10% of patients who may have been lost to follow-up, we aimed to recruit a total of 124 patients to the study. When the study finished, the missing data will be excluded.

Statistical analysis was performed using SPSS Version 15 software (SPSS, Chicago, IL, US). All statistical tests were 2 sided and significance was assumed at *P* < 0.05. Comparison of interval data was performed using independent sample *t*-tests, Mann–Whitney or Kruskal–Wallis tests when appropriate. The ROC curve analysis was performed to identify the predictive values of the BHI for POD and postoperative complications. The performance of continuous variables was analyzed with ROC curves, with the area under the curve (AUC) being calculated. Cutoff values were evaluated based on the Youden index. Relative risk (RR) and 95% confidence intervals (CIs) were estimated using a chi-squared test.

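### The postoperative BHI sample is drawn on day 1, when delirium is already being counted, so its AUC mixes concurrent with later delirium

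*Protocol article*

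**What the plan says.** The Blood Collection section schedules two BHI samples: "before the surgery in the operating room and 1 day after surgery in wards". No hour is given for the second. The Primary Outcome section states: "Investigators will assess delirium twice per day from the first to the third postoperative day in the morning and afternoon". Two of the six scheduled assessments therefore fall on the day of the second draw.

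The Hypothesis and Objectives section makes both samples index tests for the main question, namely whether BHI from "peripheral blood (preoperative or postoperative) can predict delirium after major non-cardiac surgery in elderly patients during hospitalization". The Sample Size and Statistical Analysis section covers both with one sentence: "The ROC curve analysis was performed to identify the predictive values of the BHI for POD and postoperative complications". It does not separate delirium present at the draw from delirium that begins later. The only limit stated on timing is at the late end: new onset after day 3 is taken to be unrelated to anesthetic or other intraoperative factors.

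**The concern.** A predictor should be measured before the outcome it predicts. For postoperative BHI the two windows overlap on day 1. A patient who is CAM-positive in the morning and bled later that day counts as a case for a BHI value measured after the delirium was found. In such a patient a low BHI may reflect the delirium or the acute illness behind it.

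At stake is the word predict for one of the two index tests in the main objective. The Background sets aside neuronal-damage markers because they show only a process already under way. A postoperative AUC that includes patients delirious at the draw could not be told apart from such a marker. With only 10 to 12 expected cases (9% to 11% of 112), each one carries about 8% to 10% of the weight in the AUC.

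**Working it through.** **Inputs from the Sample Size and Statistical Analysis section.** Event rate 9–11%; "a moderately good AUC of 0.8 for the BHI"; 112 evaluable patients; 90% power; two-sided alpha 0.05. The null AUC is not stated, so 0.5 is assumed.

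**The plan's own figure.** With Hanley–McNeil standard errors, power = Φ[(A1 − A0 − 1.96·SE0)/SE1]. At a 9% event rate (10 cases, 102 non-cases), SE0 = 0.0961 and SE1 = 0.0862, so power = Φ[(0.30 − 0.188)/0.0862] = Φ(1.30) = 0.90. The 112 reproduces. At 10% (11 cases, 101 non-cases) power is 0.93.

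**Inputs not in the documents (assumptions).** Let f be the share of cases already delirious at the draw; values of 10%, 20%, 30% and 50% are shown. Those cases have a BHI 1 SD lower than non-cases. Postoperative BHI carries no information on later delirium (AUC 0.50). There are 11 cases and 101 non-cases.

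**Pooled AUC.** The AUC averages over cases, so pooled AUC = f·Φ(1/√2) + (1 − f)·0.50, with Φ(1/√2) = 0.760. At f = 30%: 0.30 × 0.760 + 0.70 × 0.50 = 0.578.

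**False-claim rate.** This is the two-sided chance of rejecting AUC = 0.5 although nothing is predicted. SE0 = 0.0921. At f = 30%, SE1 = 0.0944. The upper tail is Φ[(0.078 − 0.180)/0.0944] = 0.139 and the lower tail is 0.003, together 0.14.

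**Power after the fix.** Removing the share f leaves 11(1 − f) cases against 101 non-cases, tested for AUC 0.8 against 0.5. At f = 20% there are 8.8 cases, SE0 = 0.1019 and SE1 = 0.0917, so power = Φ[(0.30 − 0.200)/0.0917] = 0.86.

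| Share f | Pooled AUC | False-claim rate | Cases left | Power after fix |
|---|---|---|---|---|
| 10% | 0.53 | 6% | 9.9 | 0.90 |
| 20% | 0.55 | 9% | 8.8 | 0.86 |
| 30% | 0.58 | 14% | 7.7 | 0.81 |
| 50% | 0.63 | 30% | 5.5 | 0.67 |

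These rates use a normal approximation. A rank-test simulation with 1, 2, 3 and 5 of the 11 cases shifted gave about 5%, 7%, 11% and 24%: somewhat lower, with the same pattern.

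**The case against.** **The share may be small.** The Background says of POD: "It commonly occurs between postoperative days 2–5". That points to few cases on day 1, and at 10–20% the illustrated distortion is slight. This stands, and it is why no single size can be claimed. It does not bring the share to zero. Because counting stops at day 3, day-1 onsets also weigh more here than they would in a window running to day 5.

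**The article does not say that such patients are counted.** It gives one sentence on ROC analysis and defines no analysis set, and a full protocol or analysis plan may do so. This stands in part: what is printed is the overlap. But the article itself fixes the draw day, the outcome window and the ROC for POD, and following them as written mixes the two kinds of case. If clock times are not recorded, no later plan can sort cases found on the day of the draw.

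**Only one predictor is touched.** Preoperative BHI is drawn before any postoperative assessment, and the Discussion's aim of finding high-risk patients before surgery rests on it. This stands. A reader might infer that the whole prediction claim fails, or that 112 is wrong because of the overlap. The documents support neither.

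**Delirium before surgery.** A reader might also infer that patients delirious at the preoperative CAM contaminate the outcome. The outcome is not expressly limited to patients CAM-negative then. But the eligibility criteria require mental competence and exclude an unstable mental state, so few if any patients would be affected. It is at most a wording note.

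**Conclusion.** The point holds for postoperative BHI only and should be fixed. That the draw and the outcome window overlap is certain from the text; the size of the effect is not. It depends on the hour of the draw and on the share of cases already delirious, and neither is given. The tabled range, from almost no distortion at 10% to a false-claim rate of 30% at a 50% share, rests on the assumed 1 SD shift and on no true prediction. Upward bias is plausible, since the Introduction describes BHI as falling with perioperative oxidative stress, but the documents do not prove it. If BHI separated cases equally well before and after onset, the AUC would not be biased numerically, yet it would still not be purely predictive. A reader who takes a large bias as shown goes beyond the documents.

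**What to change.** Record the clock times of the postoperative draw and of every CAM or CAM-ICU assessment, and do the scheduled day-1 morning assessment before the draw. For postoperative BHI, set a landmark at the draw: exclude patients positive at or before it, and count only delirium first detected afterwards. Report BHI in those already delirious separately, as association. Leave the preoperative analysis as it is.

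The practical cost is the recorded times, the order of one assessment, and a sentence in the analysis section. The statistical cost is lost events in the postoperative analysis alone, with the power shown in the table. The cost rises with the share, as the bias does: where the bias is small the fix is nearly free, and where it is large the power loss is real. Restoring 90% power for AUC 0.8 at a 10% event rate would take about 112, 126, 144 and 200 evaluable patients at shares of 10%, 20%, 30% and 50%. If the sample is not enlarged, the postoperative result should be given with its confidence interval and the number of cases after the draw.
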